### *Sensitivity and subgroup Analyses*

We will undertake various sensitivity and subgroup analyses to supplement evidence from the primary analysis to help to characterize fully the treatment effect. These will include (i) analysis by 'treatment received'; (ii) analysis of the study subgroup with a diagnosis of stroke unchanged at 90 days; (iii) others. Subgroup analyses will generally, but not exclusively, be undertaken for specific categories in factors with a significant relationship with the primary outcome measure. These analyses are either confirmatory or exploratory and, as the study is not statistically powered for multiple analyses, their results will be interpreted in this context.

### *Missing Data*

In general, we shall endeavour to adopt a consistent approach to missing data relating to both clinical and cost effectiveness, except where individual outcome measures require variation in that approach. For each variable, we shall summarise the frequency of missing data, which affects effective sample size and hence statistical power. If there is no reason to suspect that data are not Missing Completely At Random (MCAR), we shall consider the use

appropriate imputation methods to ameliorate the problem of missing data; otherwise, the Trial Statistician and Chief Investigator will further discuss patterns in missing data.

### *Reporting*

Outcome descriptions, summaries and comparisons will be expressed in accordance with appropriate CONSORT guidelines[28], including estimates with 95% confidence intervals to summarise two-tailed tests at the 5% significance level.

## **Sample size**

Sample size considerations are based on postulated and standardised statistical effects of the intervention on binary outcomes. A change from 0.1 to 0.13 (for instance, in the proportion of cases with a good mRS score at day 90) is equivalent to an effect of 0.1, while a change from 0.43 to 0.53 (for instance, in the proportion of patients receiving thrombolysis) is equivalent to an effect of 0.2.

In the initial protocol for this trial, sample size considerations assumed equal patient numbers per arm, allowed for 3% attrition for a primary outcome collected at day 90, used conventional values of 80% power and 5% significance, and a relatively small change between arms from 0.1 to 0.13 in the proportion of cases with a good mRS score at day 90, equivalent to a standardised statistical effect of 0.1. These considerations led to an initial recruitment target of 3640 (1820 cases per arm).

However, in early 2017, informal review of internal phase data showed that some key assumptions were unlikely to be met in practice. Specifically, overall recruitment was lower than anticipated, while intervention paramedic training completion rates meant a persistent imbalance in patient numbers in the two arms, with typically 8-10 control cases for every 5 intervention cases.

Following discussions with stakeholders (including both trial oversight committees and funders), it was agreed to amend the primary outcome to the proportion of patients receiving intravenous thrombolysis; postulating a change from 0.43 to 0.53 in the proportion of patients receiving thrombolysis, equivalent to a standardised statistical effect of 0.2. Sample size considerations were therefore re-assessed, factoring in attrition of 1%, power of 90% (and 5% significance), and an average cluster (patients per paramedic) of 5 with an intra-cluster correlation coefficient of 0.02. In addition, an imbalance of 2 control cases per intervention cases was incorporated. This gave a revised recruitment target of 1297 study participants (865 control cases versus 432 intervention cases).

This revised target sample size should, if underlying assumptions are satisfied, lead to 1284 analysable outcomes (856 control; 428 intervention). However, should the attrition rate or imbalance ratio change during the course of the study, it may be necessary to adjust the final sample size accordingly to achieve the required number of control and intervention analysable outcomes needed to maintain statistical power.

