| Primary outcome:    | Proportion of participants receiving intravenous thrombolysis.                                                                                                                                                                                                                                                                                                                                                                                                                                                                                                            |
| Secondary outcomes: | 

• Stroke severity and complications at 24 hrs post thrombolysis

• Inpatient mortality

• Destination at discharge and 90 days

• Dependency at discharge and 90 days

• Assistance required at discharge and 90 days

• Time from emergency call and hospital admission to first brain imaging, thrombolysis, stroke unit admission, formal swallow assessment

• Patient experiences during the intervention pathway

• Professional views of the intervention pathway

 |
| Sample size:        | 1297 participants provide 90% power to detect a 10% difference in the proportion of patients receiving thrombolysis.                                                                                                                                                                                                                                                                                                                                                                                                                                                      |
| Study duration:     | 2.5 Years.                                                                                                                                                                                                                                                                                                                                                                                                                                                                                                                                                                |

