## 5. Background

Stroke is responsible for a high global burden of mortality and disability[1]. In the UK it remains the third leading cause of death and the single largest cause of adult disability with an economic impact of approximately £4 billion per year[2].

The most widely used cost-effective emergency treatment is thrombolysis using intravenous recombinant tissue Plasminogen Activator (iv rtPA) for selected ischaemic stroke cases within 4.5 hours of symptom onset, but outcomes are highly time dependent[3] [4]. Within 60-90 minutes of symptom onset only 4 suitable patients need to be treated for one person to be free from disability, whereas at 270 minutes the same impact would require 9 patients to be treated. Despite the evidence from clinical trials, related guidelines and policy, audit continues to show large variations in the rate and speed of thrombolysis delivery between services and diurnal variations within services[5, 6]. In 2014, only 11% of total stroke admissions in the NHS were treated with thrombolysis against an aspirational target of 20%, with a median door to treatment time of 54 minutes despite a target of <40 minutes[5]. Benefits for patients and social care resources would be substantially improved if more patients were treated sooner.

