## **9. Randomisation**

PASTA is a cluster RCT in which the unit of randomisation is an ambulance station or, in the case of large ambulance stations, an identifiable paramedic team within a station. Clusters comprise the paramedics based within teams or at stations. Randomisation will be performed prior to the start of the trial in each region. Within each ambulance service, ambulance stations or paramedic teams (according to local service configuration) which feed into a study hospital will be randomised to delivering the PASTA pathway or to continue with standard stroke care. All paramedics will be given the option of not assisting with the study.

Stations or teams within each service will be stratified according to size (categorised as small, medium or large according to the personnel and resources available), and distance from the nearest study hospital admitting stroke patients (distance categorised as near or far, reflecting the local geography of each ambulance service). The use of these stratifying variables will ensure that PASTA care paramedics (intervention) and standard care paramedics (control) are approximately equally matched by operational characteristics. The actual randomisations will be performed, documented and reported by two statisticians at Swansea University Clinical Trials Unit.

Stations and teams randomised to continuing standard care will be informed that there is an ongoing study of pre-hospital assessment for stroke patients, but not be given any further information about the intervention. For paramedics who are part of a station or team randomised to deliver the PASTA pathway, study specific training and documentation will be provided. Paramedics who opt out of the study or who work within a station or team that was not selected to be involved in the study will continue to deliver standard care.

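### The 90% power is calculated with the paramedic as the cluster although stations or teams are randomised, so it is unsupported at the randomised level

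*Protocol*

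**What the plan says.** Section 9 of the protocol defines the design: "the unit of randomisation is an ambulance station or, in the case of large ambulance stations, an identifiable paramedic team within a station". It adds that a cluster is made up of the paramedics who work from that station or in that team, so a randomised unit normally holds several paramedics. Stations and teams are stratified as small, medium or large.

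The sample size part of section 18 uses a different unit. It lists "an average cluster (patients per paramedic) of 5 with an intra-cluster correlation coefficient of 0.02", together with 1% attrition, a 2:1 control-to-intervention imbalance and "postulating a change from 0.43 to 0.53 in the proportion of patients receiving thrombolysis". The result is a target of 1297 (865 control, 432 intervention), expected to yield 1284 analysable outcomes (856 and 428). Section 4 repeats the conclusion: "1297 participants provide 90% power to detect a 10% difference in the proportion of patients receiving thrombolysis".

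Section 18 foresees adjusting the final size if attrition or the imbalance ratio changes. It has no such provision for clustering. No number of stations or teams, no patients per station or team, and no station-level ICC is given.

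**The concern.** When whole stations or teams are allocated, the variance of the difference between arms depends on the correlation among all patients in the same randomised unit, not only among patients of the same paramedic. A design effect built on five patients per paramedic counts the first kind of pair (same paramedic) and gives zero weight to the second (different paramedics, same station). If that second correlation is above zero, the effective sample size is smaller than planned and the power is below 90%.

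The stated power is the justification for the amended target, which fell from 3640 to 1297 when the primary outcome was changed. If power is materially lower, a non-significant result is more likely to be read as evidence against the pathway than the data would warrant. Classing intervention paramedics by completed training, as section 18 does for the analysis, does not change which unit was randomised.

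**Working it through.** **Inputs from the protocol.** Section 18, sample size: rates 0.43 and 0.53; "power of 90% (and 5% significance"; "an imbalance of 2 control cases per intervention cases was incorporated"; attrition 1%; 5 patients per paramedic; ICC 0.02. Section 18, Reporting: two-sided, since intervals are "to summarise two-tailed tests at the 5% significance level".

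**Step 1: reproduce the stated target.** Pooled two-proportion formula with k = 0.5 intervention patients per control patient and p̄ = (0.43 + 0.5 × 0.53)/1.5 = 0.463:

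n(control) = [1.96 √(p̄(1 − p̄)(1 + 1/k)) + 1.2816 √(0.43 × 0.57 + 0.53 × 0.47/k)]² / 0.10² = 783, so 391.5 intervention and 1174.5 in total.

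- Times 1.08 = 1268.5; divided by 0.99 = 1281.3, so 1282.
- With the standardised effect of 0.2 instead: 1182.1 × 1.08 = 1276.7; divided by 0.99 = 1289.5, so 1290.

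The stated 1297 is within about 1.2% of the first and 0.5% of the second, so it reproduces.

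**Step 2: reproduce the stated power.** Effective sizes are 856/1.08 = 792.6 and 428/1.08 = 396.3. The standard errors are 0.03068 (null) and 0.03062 (alternative). Power = Φ[(0.10 − 1.96 × 0.03068)/0.03062] = Φ(1.302) = 90.4%.

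**Step 3: find the margin.** With 856 and 428 outcomes, power falls below 90% at a design effect of about 1.094. That leaves 1.094 − 1.08 = 0.014 for any correlation between paramedics of one station.

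**Step 4: design effect at the randomised level.** With m patients per station or team and 5 per paramedic, each patient has 4 companions with the same paramedic and m − 5 with another paramedic in the same unit:

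DE = 1 + (5 − 1) × ICC(paramedic) + (m − 5) × ICC(station)

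Here ICC(station) is the correlation between patients of different paramedics in one unit. The plan's 1.08 is this formula with ICC(station) = 0. To stay within the 0.014 margin, ICC(station) must not exceed about 0.014/5 = 0.0028 at m = 10, or 0.014/15 = 0.0009 at m = 20.

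**Step 5: power over assumed values.** ICC(paramedic) is kept at 0.02. The values of m and ICC(station) are assumptions, and all units are taken as equal in size. Each cell is power, with DE in brackets.

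| ICC(station) | m = 10 | m = 20 | m = 30 | m = 50 |
|---|---|---|---|---|
| 0.0025 | 90.0% (1.093) | 89.4% (1.118) | 88.7% (1.143) | 87.4% (1.193) |
| 0.005 | 89.7% (1.105) | 88.4% (1.155) | 87.0% (1.205) | 84.3% (1.305) |
| 0.01 | 89.0% (1.13) | 86.4% (1.23) | 83.6% (1.33) | 78.2% (1.53) |
| 0.02 | 87.7% (1.18) | 82.3% (1.38) | 76.9% (1.58) | 67.3% (1.98) |

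The last row assumes that patients of different paramedics at a station are as alike as patients of one paramedic. Unequal unit sizes, which the small/medium/large strata imply, would raise the design effect further.

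**Step 6: detectable difference.** With a control rate of 0.43 and the same 1284 outcomes, 90% power is reached for a difference of about 10.6 points at DE 1.23 and 12.0 points at DE 1.58.

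**The case against.** The strongest reply is that the document cannot show how far power falls, or that it falls materially. Every figure below 90% needs a cluster size and a station-level ICC that the protocol does not give. With a station ICC of 0.0025 the loss is at most about 3 points even at 50 patients per station. With a station ICC up to 0.01 and up to 20 patients per station, power is still at least 86% and the detectable difference about 10.6 points instead of 10. This stands, and it limits the finding to lack of support plus a range.

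A reader might be tempted to argue from section 5, which says that "audit continues to show large variations in the rate and speed of thrombolysis delivery between services". That does not carry the point. The variation is between stroke services, whereas section 9 randomises stations within each ambulance service among those feeding study hospitals. Stations in both arms can feed the same hospital, and differences between hospitals then largely cancel from the comparison. What matters is the residual correlation within a station, on which the protocol is silent.

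It can also be said that section 18 requires 95% confidence intervals, so a null result would not be judged on planned power alone. That softens the consequence but leaves the stated 90% without a basis.

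None of this removes the mismatch itself: the allocation unit and the unit in the calculation differ, both are stated in the protocol, and a separate analysis plan would not correct a figure that the protocol asserts.

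**Conclusion.** The concern holds as a wrong design input, the cluster level. It is not an arithmetic slip, since the target and the power both reproduce. The 90% power in sections 4 and 18 is unsupported at the level that was randomised, and it is overstated if the protocol's ICC of 0.02 applies there: 87.7% at 10 patients per station and 67.3% at 50. Over the whole assumed range (station ICC 0.0025 to 0.02, 10 to 50 patients per station, equal sizes), power runs from 90.0% to 67.3%.

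A reader might infer that true power is known to lie somewhere around 75% to 87%, or that the 0.02 row follows directly from the protocol. Neither is supported. The 0.02 is given for the paramedic level only, and patients per station are not reported, so no single corrected power or sample size can be stated from the document.

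**What to change.** Recompute the design effect at the randomised level with the formula in step 4. Use the actual number of stations and teams, the mean and variation in patients per unit, and ICCs estimated from data pooled over the arms, so that no comparison between arms is revealed. Alternatively, state and justify why correlation between paramedics of one station is negligible. Then restate in sections 4 and 18 either the power for the 10-point difference or the difference detectable with 90% power, and name the station or team as the cluster in both places.

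The cost is one recalculation and a few amended figures, and the stated power will probably look less favourable. Whether recruitment should change depends on the result and is for the sponsor and the oversight committees.

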## 19. Internal pilot study

The study will commence as an internal pilot trial involving the North East Ambulance NHS Foundation Trust and two North East hospital sites. The success of the pilot study will be judged against the following criteria after 4 months of recruitment activity:

1. > 80% of confirmed stroke admissions are assessed for study eligibility. This will be determined by comparison of the participant eligibility log data and data extracted from routine hospital systems which record stroke admissions.
2. >80% of patients identified as eligible for the study are approached about study participation.
3. Each hospital site has recruited a minimum of 4 participants/month into the study. This number is lower than an estimated predicted monthly recruitment rate for each hospital, however, the uniqueness of this study makes it difficult to precisely predict a recruitment rate until the study commences.
4. Of the participants recruited to the study who travelled with an intervention paramedic, >50% had the PASTA pathway information handover attempted.

If any of these criteria are not achieved, a review of the appropriate study procedures will be undertaken to determine why it was not possible for a criterion to be achieved. If it is believed that a change to processes will enable the study to be delivered, changes will be made and the study will continue. Decisions will be discussed and agreed with the Trial Steering Committee.

If any of these criteria are not achieved, a review of the appropriate study procedures will be undertaken to determine why it was not possible for a criterion to be achieved. If it is believed that a change to processes will enable the study to be delivered, changes will be made and the study will continue. Decisions will be discussed and agreed with the Trial Steering Committee.

## 20. Economic analysis

The primary economic analysis will be a within trial economic evaluation to estimate cost-effectiveness of the enhanced role versus usual care in increasing the proportion of patients receiving intravenous thrombolysis, and will report a cost per additional patient thrombolysed. In addition a cost utility analysis will be conducted to estimate cost per quality adjusted life years (QALYs).

To derive health outcomes at 90 days, a model based simulation will be constructed using a model previously developed which describes outcomes at 90 days based on whether or not thrombolysis was given, time elapsed since stroke onset if it was given and other physiological and demographic factors[29]. A Monte Carlo approach will be taken in which different subsets of trial participants from each arm are repeatedly sampled and their health status at 90 days is estimated. The effectiveness and cost-effectiveness of the enhanced role versus usual care will be the average of all the samples, together with an estimate of uncertainty.

Pre-stroke and 90 days mRS scores will be used to estimate QALYs using mapping algorithm which has been developed by Rivero-Arias et al. to estimate the EQ5D scores from mRS values[30]. Mortality and utility values will be converted into QALYs using the area under the curve method, controlling for baseline health utility derived from mRS[31]. The uncertainty analysis results will be presented as a cost effectiveness acceptability curve (CEAC)[32]. The CEAC will show the probability that an enhanced role is cost-effective

compared with usual care, given the observed data, for a range of maximum monetary values that decision makers may be prepared to pay for percentage change in proportion of patients that are thrombolysed /extra QALY.

*Estimating the resources used and costs of providing an enhanced paramedic role:*

The costs of paramedic time will be based on the equivalent hourly wage for the appropriate grades. The time taken to complete the training will be recorded by the computer based training software. Training material productions costs will be excluded from the evaluation. The times from the “on scene” to “handover” and “clear to respond to another incident” will be recorded and used to estimate additional ambulance service resource utilisation that may result from the enhanced paramedic role. The costs of these resources will be obtained from Ambulance Trusts and published sources including the PSSRU.

*Estimation of consequences for resource use of an enhanced paramedic roles resulting from improved stroke outcomes:*

Data on the use of NHS inpatient resources used will be collected for patients in both arms of the trial. This data will be comprised of brain imaging modality, provision of thrombolysis and length of stay in hospital. In addition, data about community rehabilitation therapy, social service involvement and non elective episodes of secondary care post discharge will also be collected. This information will be collected as part of the study day 1/2 and day 90 data collection points.

Unit costs will be derived from routine sources for NHS and social care. The costs of providing the PASTA pathway for stroke mimic patients will be included within the economic evaluations but also presented separately. This will represent an economic worst case scenario because costs will be added but it will be assumed that there is no benefit (or harm) to these individuals. If the intervention still appears cost-effective in this scenario then the trial conclusions would be strengthened.

*Missing resource use data:*

Where there is data missing about post acute resource usage, essential items will be imputed from data present in the study for similar patients as defined by age, stroke severity and 3 month outcome[33]. Sensitivity analysis will quantify the degree of bias introduced by imputation.

*Sensitivity Analyses:*

Sensitivity analyses will be conducted on key parameters and assumptions contributing the estimates of cost-effectiveness. They will be designed to estimate the robustness of the findings and to provide additional information to decision makers. For example, how estimated cost-effectiveness is affected by assumptions about the extent of the resource and financial burden on ambulance services that result from paramedics performing an enhanced role.

*Long-term economic evaluation:*

In common with other economic evaluations, a further modelling analysis will be undertaken to extrapolate the results of the trial beyond the 90 days, which will help to inform likely longer-term cost and effects. The model will be a microsimulation state transition model made up of three states (independent, dependent and death) to which costs and QALYs will be attached[34]. To estimate the longer term effects of increased independence that may result from an enhanced paramedic role in the timely treatment of stroke, the economic model will describe changes in dependency status over time. Outcomes after subsequent strokes (dependency measured by the modified Rankin Score at day 90) will be estimated

using a published decision analytic model (DAM) which predicts the outcome of treating acute stroke with and without thrombolysis[29].

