#### *Quantifying uncertainty in estimates of cost effectiveness:*

Bootstrapping will provide estimates of the imprecision surrounding estimates of costs and incremental cost per unit of outcome. Results will be presented as cost effectiveness acceptability curves (CEACS)[32]. Probabilistic sensitivity analyses will be carried out on key cost parameters. If after initial analysis it is found that the cost-effectiveness of the intervention is sensitive to one or more inputs, an Expected Value of Perfect Parameter Information (EVPPi) will be undertaken focusing on those inputs[35].

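### The economic point estimate is defined as an average over resampled subsets; read literally this averages incremental ratios, which gives a cost per QALY with no stable value

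*Protocol*

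**What the plan says.** Section 20 of the protocol (Economic analysis) names two outputs. The primary one is a within-trial evaluation that "will report a cost per additional patient thrombolysed". The second is introduced with "In addition a cost utility analysis will be conducted to estimate cost per quality adjusted life years (QALYs").

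The next paragraph begins: "To derive health outcomes at 90 days, a model based simulation will be constructed using a model previously developed". It describes a Monte Carlo approach in which "different subsets of trial participants from each arm are repeatedly sampled and their health status at 90 days is estimated", and it closes with the estimator: "The effectiveness and cost-effectiveness of the enhanced role versus usual care will be the average of all the samples, together with an estimate of uncertainty".

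Neither the size of the subsets nor whether they are drawn with replacement is given. Later in section 20, under *Quantifying uncertainty in estimates of cost effectiveness*, the protocol adds: "Bootstrapping will provide estimates of the imprecision surrounding estimates of costs and incremental cost per unit of outcome". Acceptability curves are planned in both places. Nowhere does section 20 say that the incremental ratio is one mean difference divided by another, and it does not mention net benefit.

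**The concern.** The closing sentence applies one operation, averaging over samples, to effectiveness and to cost-effectiveness alike. For effectiveness that is harmless. For cost-effectiveness the reported quantities are ratios, and the literal reading is to form a ratio in each sample and average the ratios. That estimates something other than the ratio of mean incremental cost to mean incremental effect. It is dominated by samples whose effect is near zero, and it mixes negative ratios, which can mean either dominance or being dominated, with positive ones.

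The spread across subsets raises a second problem. It depends on how large the subsets are and how they are drawn, so it is not automatically the standard error of the full-arm estimate. The later bootstrap text concerns imprecision and does not redefine the point estimate. At stake are the headline cost per QALY and possibly the headline cost per extra patient thrombolysed.

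**Working it through.** **Inputs from the protocol.** Section 18, Sample size: proportions ("postulating a change from 0.43 to 0.53 in the proportion of patients receiving thrombolysis"), error rates ("factoring in attrition of 1%, power of 90% (and 5% significance"), 5 patients per paramedic with an intra-cluster correlation of 0.02, 2 control cases per intervention case, and 856 control and 428 intervention analysable outcomes. Section 18, Reporting: two-tailed tests. Section 5: number needed to treat 4 (early) to 9 (at 270 minutes).

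**Reproducing the plan's figure.** Design effect = 1 + (5 − 1) × 0.02 = 1.08. The normal-approximation formula for two proportions gives 783 controls, so the total is 783 × 1.5 × 1.08 / 0.99 = 1281, or 1.2% below the stated 1297. Using the standardised effect of 0.2 gives 1291. The stated figures are consistent with each other (1284 / 0.99 = 1297), and power at 856 and 428 is 0.904. The planning inputs can therefore be used to fix precision.

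**Precision of the incremental effect.** SE = √[1.08 × (0.43 × 0.57/856 + 0.53 × 0.47/428)] = 0.0306. z = 0.10/0.0306 = 3.27. The chance that a sample effect is at or below zero is 0.0006.

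**Cost per extra patient thrombolysed.** The protocol gives no cost, so results are multiples of the true ratio. If incremental cost is independent of effect, mean(c/e) = mean(c) × mean(1/e), and the multiple does not depend on the cost level. The second-order approximation is 1 + 1/z² = 1.09. Simulation with normal effects, 400 runs of 10,000 samples:

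| Samples | Mean of ratios / true: median (5th–95th percentile of runs) | Ratio of means / true |
|---|---|---|
| Full arm size | 1.14 (1.03–1.26) | 1.00 (0.99–1.01) |
| Half size, with replacement (SE 0.0433, z 2.31) | 1.28 (0.24–2.60) | 1.00 (0.99–1.01) |

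Binomial resampling at full size also gave 1.14. These are typical values across runs: the average has no finite expectation once effects can reach zero.

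- *True gain of 5 points, full-size samples:* z = 1.63 and 5.1% of samples are at or below zero. Six runs of 10,000 gave 0.45 to 3.5 times the true ratio.
- *Cost linked to effect:* if c = a + b × e, then c/e = b + a/e, and only the a part is distorted. With a = 100 and b = 1000 the true ratio is 2000 and the excess is about 0.14 × 1000 = 140, or 7%. With a = 0 there is no error.
- *Negative incremental cost:* a true ratio of −1000 averaged −1174 to −1182, further below zero.

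**Cost per QALY.** The assumed inputs are 10 points more thrombolysed, utility gain 0.3 to 0.5 per disability-free patient, and utility SD 0.15 to 0.35. The 90-day time factor cancels from z.

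- Mean gain = 0.10/NNT × utility gain: from 0.10/9 × 0.3 = 0.0033 to 0.10/4 × 0.5 = 0.0125.
- SE = SD × √[1.08 × (1/856 + 1/428)] = SD × 0.0615: from 0.0092 to 0.0215.
- z runs from 0.15 to 1.35, and 44% down to 9% of samples have an effect at or below zero.
- Repeated runs of 10,000 samples gave averages from about −20 to +110 times the true ratio, with changes of sign.

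**Spread across subsets.** For a fraction f of the arm, the spread relative to the true SE is √[(1 − f)/f] without replacement: 2.0, 1.0, 0.5 and 0.33 at f = 20%, 50%, 80% and 90%. With replacement it is 1/√f, or 1.41 at f = 50%.

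**The case against.** The strongest objection is that the protocol never says a ratio is formed in each sample. Averaging costs and effects over the samples and dividing once fits the same words and is sound. That stands. It means the text admits the poor estimator without clearly ordering it. A reader might infer that the protocol's economic figures will certainly be wrong; the documents do not support that.

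The reach is also limited. The sentence ends a paragraph about 90-day health outcomes, while cost per additional patient thrombolysed is a within-trial measure that needs no such model. The 14% figure, the one closest to protocol inputs, therefore concerns the measure that the sentence covers less surely. The closing words do name cost-effectiveness of the enhanced role versus usual care, as the opening of section 20 does, so the wider reach is possible but not established.

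A reader might also infer that the cost per extra patient is overstated in general. It is not. Section 20 counts thrombolysis provision among the costs, which ties cost to effect, and counts length of stay and later care, which could make incremental cost negative.

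The QALY inputs are assumptions, and model-predicted outcomes may vary less than the SDs used here. The protocol does not say that the spread across subsets is to be the standard error, and it assigns imprecision to bootstrapping. Acceptability curves count samples with positive net benefit and divide nothing, so they are unaffected. One could add that the exact ratio estimator belongs in an analysis plan. Here, though, the protocol states a rule for the point estimate, and that rule can be judged as written.

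**Conclusion.** The estimator sentence is badly fixed: it has one sound reading and one, the more literal, that should not be used.

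On the literal reading the cost per QALY has no stable value whenever sampled effects straddle zero. That is likely across the assumed range (z from 0.15 to 1.35) but rests on utility inputs that the protocol does not give. If the sentence also governs cost per extra patient thrombolysed, the average is typically about 14% too high at the design effect, given full-size samples and a positive incremental cost independent of effect. The error is smaller if cost moves with effect and nil if cost is exactly proportional to it. For smaller effects or smaller subsets the problem is instability, with no assured direction.

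The spread across subsets depends on an unstated size and replacement rule and should not serve as the standard error. The acceptability curves limit the damage to the headline ratios. The point is worth correcting because the remedy is so cheap.

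**What to change.** Replace the closing sentence of the simulation paragraph in section 20 with text to this effect:

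*The incremental cost-effectiveness ratio is the mean incremental cost divided by the mean incremental effect. For QALYs the mean effect uses the modelled 90-day outcomes and the planned adjustment for baseline utility. Ratios from individual samples will not be averaged. Incremental net monetary benefit will be reported alongside. Resamples will be of full arm size, drawn with replacement and respecting clusters, and will be used only to describe uncertainty through the cost-effectiveness plane and acceptability curve.*

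The cost is a sentence or two of text and minor changes to the resampling code. No further data are needed.
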